#### Blinding

The study mode of the stimulation device encodes sham and active stimulation using preprogramed codes so that the participant and investigators will be blind to the type of stimulation. The stimulation parameters (duration, fade-in, fade-out time, and current intensity) are set and saved on the device to avoid accidental modification of the parameters. To investigate the success of the subject-blinding, participants will be asked about their beliefs of the received stimulation type at the last stimulation session. After completing the 6-month follow-up measurement or after dropping out of the study, participants, and their caregiver will be informed about group allocation. Participants in the sham condition will not receive active stimulation after the end of the trial. Premature unblinding using prepared envelopes can be performed when knowledge of the actual group allocation becomes necessary for the safety of the patient. The blinding, code storage, and preparation of code-break envelopes will be done by a staff member not directly involved in the intervention and the day-to-day management of the study.

#### Inclusion Criteria

Participants eligible for the trial must comply with all of the following:

MaleFulfilling ICD-10 criteria for ASD and diagnosed with ASD from a trained professional using the Autism Diagnostic Interview-Revised [ADI-R; (84)] and/or the Autism Diagnostic Observation Schedule [ADOS 2; (85)]Age between 12 and 18 yearsRight-handedIQ ≥ 70 assed using standardized instrumentsTreatment-naive to neurostimulationSigned written informed consent of the participant and primary caregiver.

#### Exclusion Criteria

Contraindications for tDCS such as cardiac pacemakers, defibrillator, cochlear implant, intracranial/cranial stimulators, and other metals in the headContraindications for MRIEpilepsy or related seizure disordersOther severe neurologic or psychiatric disorders or medical conditions (e.g., skull defect and craniotomy)Concomitant psychopharmacological medication.

Ongoing concomitant social or psychotherapeutic long-term interventions must be held constant during the course of the intervention.

### Intervention

The intervention phase comprises 10 sessions of tDCS or sham stimulation within two consecutive weeks, with a 2-day break after the fifth session (see Figure 1 for study overview). If feasible for the participant, all stimulation sessions will be held at the same time of the day. In each session, prior to the stimulation, the participant will complete a brief questionnaire about general well-being, attention, motivation, and experiences before the session. Afterwards, two rubber electrodes with conductive paste will be attached to the head of the participant. To decide on the optimal stimulation parameters, an MRI-based finite-element model approach was utilized, which simulates the intensity, distribution, and focality of the electric field induced by tDCS. To this aim, SimNIBS 3.1 (86) and structural T1 images of adolescents with ASD from a previous clinical trial executed by our research group were used. The parameters under comparison comprised an intensity of 2 mA, three different electrode sizes (3 × 3, 5 × 5, and 5 × 7 cm rectangular rubber electrodes) and two different conductors (NaCl solution and Ten20 paste).

**Figure 1 F1:**
[figure not shown]
Study timeline and overview. After enrollment, participants will undergo a set of psychological, behavioral, and physiological baseline measures in the first week. Following randomization, 10 sessions of either active or sham tDCS will be conducted within a 2-week interval. Post-treatment measures are repeated on the subsequent week. Two follow-up measures are planned 1 and 6 months after the end of the tDCS intervention. ERT, emotion recognition task; FEFA II, frankfurter test and training for recognizing facial affect; FHA, frith-happé animations; MASC, movie for the assessment of social cognition.

Simulations demonstrated peak intensity of electric fields showing stronger fields with smaller electrodes (3 × 3 cm) and conductive Ten20 paste. Here, stimulating anodal tDCS over the left DLPFC would lead to peak magnitudes at the MPFC (see Figure 2), which match with the targeted neural circuit. This stimulation setup is in line with the recommendations suggested in a recent systematic review and meta-analysis on the existing literature of tDCS in ASD (77) and with other studies demonstrating effects of tDCS on reducing ASD symptoms. Therefore, an electrode montage with the anode over the left DLPFC (F3 according to the international 10-20 system for EEG) and the cathode over the right supraorbital region will be used in the current trial.

**Figure 2 F2:**
[figure not shown]
Four examples of the simulations of our tDCS protocol in adolescents using SimNIBS and previously acquired T1-weighted MRI scans of a comparable population. The electric field was simulated using bilateral montages (anode at F3 and cathode Fp2-supraorbital), an intensity of 2 mA, and three different electrode sizes. Each row represents one participant and each column represents one montage. Peak magnitudes of the intracranially generated electric fields are listed below each simulated configuration.

To localize the electrode site F3, the Beam F3 system (87) will be used. Anodal tDCS will be administered through an Eldith-DC Stimulator (NeuroConn GmbH, Germany) at 2 mA current strength for 20 min with a fade-in and fade-out of 30 s at the start and end of the stimulation. During the sham stimulation, a fade-in phase of 30 s, followed by 40 s of 2 mA stimulation and a fade-out phase of 30 s will be applied. The participants will experience the typical skin sensation usually produced at the beginning of an active tDCS stimulation and are therefore expected to remain unaware of the real condition (88).

#### Safety and Adverse Events

As for potential risks of tDCS, guidelines report no serious adverse events in over 18,000 sessions of low-intensity transcranial electrical stimulation in pediatric and adult patients, as well as in healthy subjects (89). Current data also specifically emphasize the feasibility, tolerability, and safety of tDCS in children and adolescents (45, 63, 90). Adverse effects of tDCS in children and adolescents were described as mild and transient, including tingling (11.5%), itching (5.8%), redness (4.7%), and scalp discomfort (3.1%) (91). Thus, when guidelines are followed, tDCS is a safe modality for children and adolescents with various neurological conditions (92). The proposed parameters of this study (including electrode size, current strength, and duration) were previously tested for their safety in children younger than the participants in this study (93, 94). The brain stimulation device will be operated by experienced psychologists, neuroscientists, and research assistants trained in the application. Therefore, no serious adverse events or serious health risks for the participants of this study are expected. In the case of a serious adverse event, the participant will be excluded from the trial and the adverse event will be reported to the ethics committee of the Medical University of Vienna and to the Austrian Agency for Health and Food Safety (AGES). To protocol adverse effects, the German version of the questionnaire of sensations related to transcranial electrical stimulation will be used at the last stimulation session (accessible at: http://neurologie.uni-goettingen.de/downloads.html).

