## Abstract

**Background:** Social–emotional difficulties are a core symptom of autism spectrum disorder (ASD). Accordingly, individuals with ASD have problems with social cognition such as recognizing emotions from other peoples' faces. Various results from functional magnetic resonance imaging and electroencephalography studies as well as eye-tracking data reveal a neurophysiological basis of these deficits by linking them to abnormal brain activity. Thus, an intervention targeting the neural origin of ASD impairments seems warranted. A safe method able to influence neural activity is transcranial direct current stimulation (tDCS). This non-invasive brain stimulation method has already demonstrated promising results in several neuropsychiatric disorders in adults and children. The aim of this project is to investigate the effects of tDCS on ASD symptoms and their neural correlates in children and adolescents with ASD.

**Method:** This study is designed as a double-blind, randomized, and sham-controlled trial with a target sample size of 20 male participants (aged 12–17 years) diagnosed with ASD. Before randomization, the participants will be stratified into comorbid depression, comorbid ADHS/conduct disorder, or no-comorbidity groups. The intervention phase comprises 10 sessions of anodal or sham tDCS applied over the left prefrontal cortex within 2 consecutive weeks. To engage the targeted brain regions, participants will perform a social cognition training during the stimulation. TDCS-induced effects on ASD symptoms and involved neural circuits will be investigated through psychological, neurophysiological, imaging, and behavioral data at pre- and post-measurements. Tolerability will be evaluated using a standardized questionnaire. Follow-up assessments 1 and 6 months after the intervention will examine long-lasting effects.

**Discussion:** The results of this study will provide insights into the changeability of social impairments in ASD by investigating social and emotional abilities on different modalities following repeated sessions of anodal tDCS with an intra-simulation training. Furthermore, this trial will elucidate the tolerability and the potential of tDCS as a new treatment approach for ASD in adolescents.

**Clinical Trial Registration:** The study is ongoing and has been registered in the German Registry of Clinical Trials (DRKS00017505) on 02/07/2019.

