Within this project, it will also be monitored how the participants react to the stimulation using the questionnaire of sensations related to transcranial electrical stimulation. Even though the safety of tDCS in pediatric populations has been demonstrated repeatedly (92), information about how this patient group perceives and tolerates the mild adverse events of tDCS seems warranted. Individuals with ASD often suffer from sensory hypersensitivity (135) and may thus respond differently to the stimulation.

In this trial, a standard bipolar tDCS montage will be used with the anode placed over the DLPFC targeting the MPFC. However, other montages or stimulation methods such as multi-electrode tDCS or repetitive transcranial magnetic stimulation (rTMS) are also of interest for this population. Here, this established bipolar direct current protocol was chosen as it has milder side effects, has no history of reported serious adverse effects, and is noiseless compared to rTMS (91, 92, 136, 137). Therefore, it might be better tolerated in individuals with ASD, and participants will not be distracted from the intra-stimulation training by potentially painful sensations or sound. Regarding the usage of tDCS as a clinical treatment, a bipolar tDCS has the advantage of being more affordable, portable, and easy to administer, and it opens the possibility for home use in the future. A comparison of the effects of different stimulation protocols as well as stimulation sites is an essential element for future studies.

During the intervention, participants will have daily contact with the study team and undergo the intra-stimulation training. Although these factors could have a beneficial effect on ASD symptoms and emotion recognition skills, the double-blind design and randomization to either active or sham tDCS treatment should mitigate this potential bias.

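### The only tolerability form is given at the last stimulation session, with no stated provision for early stoppers, so the non-serious tolerability result rests mainly on those who completed the course

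*Protocol article*

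**What the plan says.** The Abstract makes tolerability part of what the trial will deliver: "Tolerability will be evaluated using a standardized questionnaire", and "this trial will elucidate the tolerability and the potential of tDCS as a new treatment approach for ASD in adolescents". The Discussion gives the reason. Sensory hypersensitivity is common in ASD and could change the response to stimulation, so "information about how this patient group perceives and tolerates the mild adverse events of tDCS seems warranted".

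Safety and Adverse Events states the purpose of the instrument ("To protocol adverse effects, the German version of the questionnaire of sensations") and its timing: the "questionnaire of sensations related to transcranial electrical stimulation will be used at the last stimulation session". The Discussion names the same questionnaire, and the article describes no other tolerability instrument.

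Under Intervention, "The intervention phase comprises 10 sessions of tDCS or sham stimulation within two consecutive weeks". A form is completed at each of them, but before the current is applied: "In each session, prior to the stimulation, the participant will complete a brief questionnaire about general well-being". Its other topics are attention, motivation and what happened before the session.

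Three further statements bear on the point. Serious adverse events lead to exclusion and to reports to the ethics committee and the national agency (Safety and Adverse Events). Dropout is foreseen, since those who leave are told their allocation (Blinding). Data collection continues until 20 participants have completed all 10 sessions and the pre- and post-measurements (Trial Status).

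**The concern.** A tolerability summary should describe everyone exposed to the stimulation. People who find the sensations hard to bear are the most likely to leave before session 10. If the form is offered only at the final session, they may never complete it, and recruitment continues until completers fill the target. The group the Discussion says it wants to learn about would then be under-represented in the answer.

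There is a second, smaller weakness. For those who finish, one form stands for 10 sessions, and the article does not say whether it asks about that day or about the whole course.

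At stake is a reassuring statement on how adolescents with ASD tolerate repeated tDCS, drawn largely from those who tolerated all of it. The efficacy result does not depend on this form.

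**Working it through.** The article states no tolerability figure that could be reproduced. The check sets its statements side by side and adds simple arithmetic.

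**Inputs**
- Sessions per participant: 10 (Intervention).
- Completers sought: 20 (Trial Status).
- Administrations of the sensations form: 1, at the last session (Safety and Adverse Events).
- Dropout rate: not given. A range of 5%, 10% and 20% is assumed here.

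**Step 1: is there another source for non-serious effects?** The form used at every session precedes stimulation and does not ask about sensations during it. The serious adverse event route does not cover tingling, itching or discomfort. No other record of non-serious effects is described.

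**Step 2: who reaches the form?** Read as the end of the 10-session course, the form reaches completers. With dropout proportion d before the last session, the number to enrol for 20 completers is 20 / (1 − d), rounded up.

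| Assumed d | 20 / (1 − d) | Enrolled | Without a form | Share of enrolled |
|---|---|---|---|---|
| 5% | 21.05 | 22 | 2 | 2/22 = 9% |
| 10% | 22.2 | 23 | 3 | 3/23 = 13% |
| 20% | 25 | 25 | 5 | 5/25 = 20% |

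Rounding up makes the first two shares larger than d. These counts cover stopping for any reason; how many would stop because of sensations is unknown. With no early stopping, the selection is zero. The Randomization section speaks of 20 participants in total. If that figure were binding, early stoppers would reduce the number of forms below 20 instead of being made up, and they would still have none.

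**Step 3: what does the form cover for completers?** There are 20 × 10 = 200 sessions among 20 completers, and 20 forms.
- If the form asks about that session only, 20/200 = 10% of sessions have a record and 180 have none.
- If it looks back over the course, all 200 are covered, but by recall. With daily sessions and the stated 2-day break after the fifth, the course spans 5 + 2 + 5 = 12 days, so the first session is recalled after 11 days.

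The article gives only a web address for the form, so it does not settle which case applies. Early stoppers lack a form in both.

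**The case against.** The strongest reply has five parts.

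- **The article is condensed.** Adverse-event logs and reasons for withdrawal may well be in the full protocol. This stands, and a reader should not infer that someone who stops because of sensations disappears from the trial's records. The Blinding section shows that those who leave are known to the team. What the article does fix is the timing of the tolerability form, and that timing is the point here.
- **Tolerability is a minor aim.** It is absent from the study goals in the Introduction and from the Outcomes section. That limits the weight of the point, but the Abstract still promises a result.
- **The form may look back over the course.** It may. A reader might infer that sessions 1 to 9 go unmeasured; the documents do not support that, because the recall period is not given.
- **The last session may mean each participant's last attended one.** The text does not say so, and an unplanned stop is often known only after that session has ended.
- **Repeated questions about sensations could draw attention to a cue to allocation.** This is a fair cost of asking after every session. It hardly applies to a single form at stopping.

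Two further inferences are tempting. One is a larger bias in the active arm: sham gives 40 s at 2 mA against 20 min in the active arm, so this is plausible, but nothing in the article shows it, and sham is meant to produce the same initial skin sensation. The other is that participants habituate by session 10, for which the article offers no evidence. The adverse-effect percentages cited under Safety and Adverse Events cannot be turned into a share of effects missed either, because their unit (session or participant) is not stated.

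**Conclusion.** The point holds within limits. As written, the result on non-serious tolerability comes mainly from participants who tolerated the full course, and for them from one end-of-course form with an unstated recall period. It can therefore lean towards good tolerability.

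The size depends on early stopping, for which the article gives no figure: 2 to 5 participants without a form at an assumed 5% to 20%, and none if nobody stops. This assumes that the last session means the end of the planned course and that all stopping occurs before it.

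It would go too far to call the trial's safety evidence as a whole biased, since serious adverse events are captured separately. The primary SRS analysis is not affected. The point merits a short amendment because a stated aim is measured in a way that favours a reassuring answer and the remedy is cheap.

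**What to change.** 1. **At stopping.** Give the same questionnaire to anyone who discontinues, at the point of stopping and before allocation is disclosed to them under the Blinding section. This deals with the selection.
2. **In the report.** Summarise tolerability by arm for all participants who received at least one session, with the number who stopped and their reasons. State the form's recall period.
3. **Preferably, after each session from now on.** Give the short form at the end of every remaining session, and label participants already treated as last-session-only.

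The form exists and participants already attend and complete paperwork at each session, so the cost is a brief amendment and a few minutes per session. The downsides are partial coverage of those already treated and, for item 3, a possible small effect on participant blinding. The blinding question already planned for the last session can check that, though only coarsely with 20 participants. If the sponsor judges the blinding risk too high, items 1 and 2 can be adopted alone.

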### Instruments

In accordance with the complexity of the disorder, the effects of the tDCS intervention will be investigated at three different levels:

Psychological ratings to detect changes in ASD symptoms as well as in comorbid symptoms;Neurophysiological measures to detect changes in brain responses to emotional stimuli;Behavioral tests to detect changes in responses and gaze behavior.

#### Psychological Ratings

Clinical information *via* questionnaires will be collected from participants and caregivers following a multi-perspective approach. The Social Responsiveness Scale [SRS; (83)] reliably indicates the presence and severity of social impairment in ASD and correlates with real-world dysfunctional behaviors. Five subscales (social awareness, social cognition, social communication, social motivation, restricted interests and repetitive behavior) and a total score will be calculated. Additionally, various instruments targeting different aspects of ASD symptoms [Autism Treatment Evaluation Checklist—ATEC (95); Social Communication Questionnaire—SCQ (96)] will be used for pre-, post-, and follow-up assessments. Furthermore, affective and cognitive components of empathy and emotion regulation abilities will be measured *via* self-reports [Emotion Regulation Questionnaire—ERQ (97); Index of Empathy for Children and Adolescents—IECA (98); Basic Empathy Scale—BES (99)] and parental questionnaires [Griffith Empathy Measure—GEM (100); Emotion Regulation Checklist—ERC (101)]. For subgroup stratification and the investigation of comorbid symptoms of ASD such as attention deficit, anxiety, aggression, and depression, the Diagnostic System for Mental Disorders in Childhood and Adolescence for ADHD, Depression, Anxiety, and Conduct Disorder [DISYPS III ADHS, DEP, ANG, SSV—self- and parental rating versions; (102)] will be used.

#### Behavioral Tests

**Frankfurter test and training for recognizing facial affect (FEFA II):** This computer-based program was developed to train and reliably test the recognition of facial affect in individuals with high-functioning ASD (103). Participants are asked to identify the six basic emotions and neutral expressions presented in 50 black-and-white photographs of faces. The stimuli used are based on Ekman's conceptualization of basic emotions (104). Correct classification and reaction times are measured.

**Movie for the assessment of social cognition (MASC):** The German version of the MASC (105) is a reliable and sensitive naturalistic measure of social cognition and gaze behavior in adolescents with ASD (106). The MASC consists of a film showing two females and two males having a dinner party. The film lasts about 15 min and is paused 43 times to ask questions about the actors' emotions, thoughts, and intentions. The revised MASC score is a measure of the degree of social cognition adopted for adolescents and will be calculated from the correct responses (106). Additionally, eye-tracking data of the participants' gaze behavior will be recorded during the presentation of the movie using the Tobii Pro eye-tracker (Tobii Group, Danderyd, Schweden) and Tobii Studio 3.4.5 (107).

**Emotion recognition task (ERT):** This self-developed task uses videos of faces and social scenes depicting different emotional states to investigate emotion recognition skills. The task involves three parts (see Figure 3 for a graphical illustration) addressing different emotion recognition competencies: (a) shows videos of one person expressing a basic or complex emotion; (b) is more challenging and presents a more naturalistic scenario in which two or more people engage in an emotional and dynamic social scene; (c) consists of morphing videos (displaying a face transitioning from a neutral expression to a basic emotion) and participants will be instructed to interrupt the morphing process as soon as they recognize the displayed emotion. Afterwards, participants will be asked to classify the emotion that was displayed in the video. The emotional stimuli represent all age groups and genders equally and are taken from validated databases. Parts (a) and (b) use stimuli form the EU Emotion Stimuli Set (108, 109), while part (c) uses stimuli from the FACES Database (110, 111). This task was implemented in Python (version 3.6.7) using the PyQt (version 5.15.2) graphics library. The ERT will be employed in pre- and post-measurements to examine changes in correct classifications and response times and to investigate pre–post changes in gaze behavior using the Tobii Pro eye-tracker (Tobii Group, Danderyd, Schweden).

